#### Effect evaluation

##### Effectiveness of the intervention

Differences in the change scores between the intervention group and the control group on the primary and secondary outcomes will be analysed with multilevel (mixed-model) linear regression analyses taking all three measurements into account (baseline, and at 4 and 12 months). We will use a model with a random intercept and all other variables fixed.

A sensitivity analysis will be performed by replacing missing values by multiple imputation. *P* values < 0.05 are considered statistically significant.

Differences in the change scores between the cohort study group and both the intervention group and the control group on the primary, secondary and other study parameters will be analysed with multilevel (mixed-model) linear regression analyses, taking all three measurements into account. We will perform subgroup analyses for severity, duration and number of the symptoms and comorbidity to explore which patients are most likely to benefit from the intervention.

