**Methods:**

A randomised effectiveness trial with an economic evaluation in primary care with 158 patients aged 18 years and older who are frequently consulting their GP with MUS. Patients will be assigned to psychosomatic therapy in addition to usual care or usual care only. Psychosomatic therapy is a multi-component and tailored intervention, aiming to empower patients by applying psycho-education, relaxation techniques, mindfulness, cognitive approaches and/or graded activity. Patients assigned to the psychosomatic therapy receive 6 to 12 sessions of psychosomatic therapy, of 30–45 min each, delivered by a specialised exercise or physical therapist.

Primary outcome measure is patient-specific functioning and disability, measured with the Patient-Specific Functional Scale (PSFS). Secondary outcome measures are symptom severity, consultation frequency and referrals to secondary care, patient satisfaction, quality of life and costs. Assessments will be carried out at baseline, and after 4 and 12 months.

An economic evaluation alongside the trial will be conducted from a societal perspective, with quality-adjusted life years (QALYs) as outcome measure. Furthermore, a mixed-methods process evaluation will be conducted.

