### Sample size and power calculation

The main aim of our study is to establish whether, compared to usual care, psychosomatic therapy improves daily functioning, disability and symptoms, while reducing costs.

Calculations of sample size are based on a minimally relevant difference (mrd) between the two arms of 1 point on the PSFS (range 0–10) [32], with a standard deviation (sd) of 2 points, with an alpha of 0.05 and a power of 0.80. With an estimated dropout rate of 20% after 1 year at least 79 patients per treatment arm need to be included. With this sample size, we can also detect differences in perceived symptom severity (measured on a visual analogue scale (VAS); mrd = 1.3; sd = 2.6) and number of consultations (mrd = 3; sd = 4).

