## Methods: assignment of intervention

### Allocation and blinding

We will use Castor EDC for the online measurements and for randomisation of the participants [48]. Castor EDC uses a variable block randomisation method and randomly assigns participants to one of the two groups, the allocation ratio will be 1:1. The randomisation sequence is masked for study personnel. In order to balance the size of the intervention and usual care groups in each region, randomisation will be stratified according to regions (Amsterdam or Nijmegen). Patients will be included in either the intervention group or the usual care group based on the random allocation. The research assistant will give all patients a unique patient identification number, matching with the corresponding name to inform each participant about the allocation. All patients will be informed about the allocation by the research assistant by regular mail. Patients randomised to the psychosomatic therapy group will also be informed about the psychosomatic therapy by telephone by the research assistant and will receive a referral from their GP to one of the psychosomatic therapists participating in this study. If patients are randomised to the usual care group, they will be offered to receive psychosomatic therapy after completion of the study if still indicated. The research assistant will inform all GPs about the inclusion and allocation of their patients by regular mail or secure e-mail.

Since psychosomatic therapy is a face-to-face intervention, patients and therapists cannot be blinded to allocation. The data analysts will not be blinded to treatment assingments, as this would be unfeasible because they are also involved in data collection.

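### The primary analysis compares PSFS change scores with no stated baseline adjustment; read naturally, this is unbiased but less precise than the baseline data allow

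*Protocol article*

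**What the plan says.** Under Effectiveness of the intervention, the protocol article states that "Differences in the change scores between the intervention group and the control group on the primary and secondary outcomes will be analysed" by multilevel linear regression on the baseline, 4-month and 12-month measurements. The model has a random intercept, and everything else is fixed. The fixed effects are not listed. The same paragraph describes the comparison of the non-randomised cohort with each trial arm in nearly the same terms.

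The Primary outcome section defines the outcome as mean change from baseline at 4 and 12 months. Allocation and blinding stratifies the randomisation by region, with two levels.

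The Sample size section plans for a "minimally relevant difference (mrd) between the two arms of 1 point on the PSFS", "with a standard deviation (sd) of 2 points", and "with an alpha of 0.05 and a power of 0.80". It then says: "With an estimated dropout rate of 20% after 1 year at least 79 patients per treatment arm need to be included". It does not say whether the SD belongs to a single PSFS score or to the change in PSFS, and it gives no correlation between baseline and follow-up.

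**The concern.** Baseline can enter a three-measurement random-intercept model in two ways. If each arm has its own baseline mean, the treatment effect at a follow-up is the difference between arms in mean change. If the arms share one baseline mean, which randomisation justifies, the effect is in substance the baseline-adjusted difference. The article fixes the contrast as a difference in change scores and says nothing about a shared mean or a covariate. Because it uses the same wording for the cohort, where a shared mean would be unjustified, free means per arm is the natural reading.

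What is at stake is precision. A change score subtracts the whole baseline value, although the follow-up score is only partly predicted by it. The weaker the correlation, the more noise this adds. With the sample fixed at 158 patients and 20% expected dropout, adjustment recovers power without recruiting anyone.

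**Working it through.** **Inputs.** From the Sample size section: difference 1, SD 2, alpha 0.05, power 0.80, dropout 20%, 79 per arm. Assumed: a two-sided test, equal variances at each visit, complete data on 63 patients per arm, and a baseline-to-follow-up correlation rho of 0.3, 0.5 or 0.7.

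**The plan's own figure.** n = 2 × (1.96 + 0.842)² × 2² / 1² = 62.8, so 63 per arm. 63 / 0.8 = 78.75, so 79. The stated number reproduces. Power with 63 per arm: SE = 2 × √(2/63) = 0.356; 1/0.356 − 1.96 = 0.85; power 0.80.

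**Variances at one follow-up**, with score variance σ²:
- change score: 2(1 − rho)σ²
- baseline-adjusted: (1 − rho²)σ²
- ratio, adjusted to change: (1 − rho²) / [2(1 − rho)] = (1 + rho)/2

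**Power with 63 per arm and a difference of 1** (normal approximation):

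| | rho 0.3 | rho 0.5 | rho 0.7 |
|---|---|---|---|
| Variance ratio, adjusted/change | 0.65 | 0.75 | 0.85 |
| *SD 2 is the SD of change* | | | |
| Change score: SD, power | 2.00, 0.80 | 2.00, 0.80 | 2.00, 0.80 |
| Adjusted: SD = 2√[(1+rho)/2], power | 1.61, 0.94 | 1.73, 0.90 | 1.84, 0.86 |
| *SD 2 is the SD of a single score* | | | |
| Change score: SD = 2√[2(1−rho)], power | 2.37, 0.66 | 2.00, 0.80 | 1.55, 0.95 |
| Adjusted: SD = 2√(1−rho²), power | 1.91, 0.84 | 1.73, 0.90 | 1.43, 0.98 |

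**Check in the three-measurement model.** I computed the generalised least squares standard error of the 12-month contrast under a random-intercept covariance with score SD 2. With free baseline means it is 0.422, 0.356 and 0.276 at rho 0.3, 0.5 and 0.7, which gives the change-score powers above. With a common baseline mean it is 0.340, 0.309 and 0.255, which gives the adjusted powers. What matters is therefore how the baseline mean is handled. Having baseline among the outcomes does not by itself bring the gain.

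**Where 80% power depends on rho.** If SD 2 is the score SD and one follow-up is tested, the change SD is at most 2 when 2(1 − rho) ≤ 1, that is rho ≥ 0.5. If the effect is averaged over both follow-ups, the change variance is 1.5(1 − rho)σ² and the threshold is rho ≥ 1/3. If SD 2 is the SD of change at the follow-up tested, there is no threshold.

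**The case against.** The strongest reply is that the article does not exclude adjustment. It lists no fixed effects, it includes baseline in the model, and the same model with a common baseline mean would be as efficient as analysis of covariance. A covariate list is often left to the full protocol or analysis plan. This stands in part: the article leaves room for the efficient version. But it does fix the contrast as a difference in change scores, and an analysis plan that followed it literally would give the less precise analysis.

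A reader might infer that the trial is underpowered unless rho reaches 0.5. The documents do not support that. The outcome is defined as change from baseline, so SD 2 may well be the SD of change, and then the stated power holds at any rho. The threshold also falls to 1/3 if the two follow-ups are averaged. Even under the single-score reading, change-score power is 0.95 at rho 0.7.

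A reader might also infer bias from chance baseline imbalance or regression to the mean. Under randomisation these add variance to the change-score contrast, not systematic error.

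Nor can the article be faulted for leaving region out. It neither includes nor excludes region, and nothing in it allows the precision lost to be calculated.

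**Conclusion.** The point holds as one of precision. The planned comparison, read naturally, is valid but gives up precision at every correlation below 1: adjustment lowers the variance by 35%, 25% and 15% at rho 0.3, 0.5 and 0.7. Power rises from 0.80 to between 0.86 and 0.94 if SD 2 is the SD of change, and from 0.66–0.95 to 0.84–0.98 if it is the SD of a single score and one follow-up is tested. Only under the latter reading does the stated 80% require rho of at least 0.5.

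These figures rest on an assumed rho, equal variances, 63 completers per arm and free baseline means per arm. The recommendation survives either reading of the SD. Region is a minor addition.

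**What to change.** - Model PSFS at 4 and 12 months with baseline PSFS as a covariate, or all three measurements with a common baseline mean for the two randomised arms. Include time, treatment-by-time and, because randomisation is stratified by it, region as fixed effects.
- Treat each continuous secondary outcome in the same way, with its own baseline.
- Do not apply the common-baseline constraint to the cohort comparisons, which are not randomised.
- State in the sample size section whether the 2 points is the SD of a single score or of change.

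The cost is wording only. PSFS is already measured at baseline and region is known from randomisation, so no extra data or patients are needed.

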### Outcome measures

#### Primary outcome

In order to estimate the primary outcome of the treatment we will measure patients’ level of specific functioning and disability measured with the PSFS. The PSFS is a self-reported, thoroughly validated, responsive measurement instrument for up to three individual activities for which patients perceive limitations rated on an 11-point numeric rating scale (NRS) ranging from 0–10 (0 representing ’impossible‘ and 10 ’not a problem at all‘) [24, 31–33]. We will measure mean change from baseline at 4 and 12 months’ follow-ups.

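### The random-intercept-only model ties the standard errors of the 4- and 12-month change contrasts to an equal-variance, equal-correlation assumption that may misstate them in either direction; an unstructured covariance removes the dependence cheaply

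*Protocol article*

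**What the plan says.** The section Effectiveness of the intervention in the protocol article specifies a multilevel linear regression for the primary and secondary outcomes, "taking all three measurements into account (baseline, and at 4 and 12 months"). It then fixes the random part: "We will use a model with a random intercept and all other variables fixed". It names no residual covariance structure, visit-specific variance or robust standard error, and does not say at which level the intercept sits. The significance rule is that P "values < 0.05 are considered statistically significant".

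The section Primary outcome defines the target as change at both follow-ups: "We will measure mean change from baseline at 4 and 12 months’ follow-ups". Neither section makes 12 months the sole primary contrast.

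The section Sample size and power calculation gives a single standard deviation, "with a standard deviation (sd) of 2 points, with an alpha of 0.05 and a power of 0.80". It does not say whether this applies to a score at one visit or to a change, and it gives no correlation between visits.

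**The concern.** A patient-level random intercept with ordinary independent, constant-variance residuals implies compound symmetry: one variance for all three visits and one correlation for all three pairs. The visits are unequally spaced, with gaps of 4 and 8 months, and baseline to 12 months is the longest interval. Baseline also precedes treatment, whereas both follow-ups come after its planned start. A lower correlation between baseline and 12 months than between neighbouring visits would be unremarkable.

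If the assumption fails, the model still pools all within-patient variation into one residual variance and applies it to every change contrast. The estimated difference between arms with complete data is unaffected, but its standard error, confidence interval and P value are not. The same model serves all secondary outcomes. The one sensitivity analysis stated for it, multiple imputation, deals with missing values and leaves this restriction in place.

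**Working it through.** **1. The plan's own figure.** Inputs from Sample size and power calculation: "minimally relevant difference (mrd) between the two arms of 1 point on the PSFS (range 0–10"), SD 2, alpha 0.05 (two-sided assumed), power 0.80. n per arm = 2 × (1.960 + 0.842)² × 2² / 1² = 62.8, so 63. With 20% dropout, 63 / 0.80 = 78.75, so 79, which matches "With an estimated dropout rate of 20% after 1 year at least 79 patients per treatment arm need to be included". This calculation does not use the repeated-measures covariance, so the present point leaves it unchanged.

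**2. What the model does.** Assume a patient intercept, independent residuals with constant variance, visit as a category with an arm-by-visit interaction, and complete data. Write V(i,j) for the variance of the difference between visits i and j within a patient:

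V(i,j) = SDi² + SDj² − 2 × r(i,j) × SDi × SDj.

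With three visits, the within-patient sum of squares is one third of the sum of the three squared differences and carries 2 degrees of freedom per patient. Twice the residual variance therefore estimates Vmean, the mean of V(0,4), V(0,12) and V(4,12). With n per arm, the model gives each change contrast the variance 2 × Vmean / n. The true variance is 2 × V(0,12) / n at 12 months and 2 × V(0,4) / n at 4 months. Hence

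- SE ratio (model / true) = √(Vmean / V)
- actual alpha = 2 × [1 − Φ(1.96 × SE ratio)]

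**3. Range under assumed covariances.** The article supplies only SD 2; every correlation and every other SD below is an assumption. SDs are in the order baseline/4/12 months and correlations in the order 0–4, 0–12, 4–12 months.

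| SDs | Correlations | V(0,4) | V(0,12) | V(4,12) | Vmean | 12-month SE ratio | 12-month alpha | 4-month SE ratio | 4-month alpha |
|---|---|---|---|---|---|---|---|---|---|
| 2/2/2 | 0.5/0.5/0.5 | 4.00 | 4.00 | 4.00 | 4.00 | 1.000 | 0.050 | 1.000 | 0.050 |
| 2/2/2 | 0.5/0.4/0.5 | 4.00 | 4.80 | 4.00 | 4.27 | 0.943 | 0.065 | 1.033 | 0.043 |
| 2/2/2 | 0.5/0.4/0.6 | 4.00 | 4.80 | 3.20 | 4.00 | 0.913 | 0.074 | 1.000 | 0.050 |
| 2/2/2 | 0.5/0.4/0.65 | 4.00 | 4.80 | 2.80 | 3.87 | 0.898 | 0.079 | 0.983 | 0.054 |
| 2/2/2 | 0.4/0.3/0.7 | 4.80 | 5.60 | 2.40 | 4.27 | 0.873 | 0.087 | 0.943 | 0.065 |
| 2/2/2 | 0.7/0.343/0.49 | 2.40 | 5.26 | 4.08 | 3.91 | 0.863 | 0.091 | 1.277 | 0.012 |
| 1.5/2/2.5 | 0.5/0.35/0.6 | 3.25 | 5.88 | 4.25 | 4.46 | 0.871 | 0.088 | 1.171 | 0.022 |
| 1.5/2/2 | all 0.5 | 3.25 | 3.25 | 4.00 | 3.50 | 1.038 | 0.042 | 1.038 | 0.042 |
| 2/2/1.5 | all 0.5 | 4.00 | 3.25 | 3.25 | 3.50 | 1.038 | 0.042 | 0.935 | 0.067 |
| 2/2.5/2 | all 0.5 | 5.25 | 4.00 | 5.25 | 4.83 | 1.099 | 0.031 | 0.959 | 0.060 |
| 2/2/2 | 0.4/0.5/0.4 | 4.80 | 4.00 | 4.80 | 4.53 | 1.065 | 0.037 | 0.972 | 0.057 |
| 2/2/2 | 0.4/0.5/0.6 | 4.80 | 4.00 | 3.20 | 4.00 | 1.000 | 0.050 | 0.913 | 0.074 |

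Rows 2 to 7 have the lowest correlation between baseline and 12 months; their 12-month SE is 5.7% to 13.7% too small. Rows 8 to 11 go the other way. The last row is not compound symmetric, yet its 12-month test is nominal.

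In points on the scale, row 3 with 63 per arm gives a model SE of √(2 × 4.00 / 63) = 0.356 against a true SE of √(2 × 4.80 / 63) = 0.390.

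**4. Check with dropout.** REML fits of the random-intercept model were simulated under no effect with 79 per arm, 10% missing at 4 months and 20% at 12 months, completely at random, 2,500 runs per cell (simulation error about √(0.05 × 0.95 / 2500) = 0.004). Rejection rates at 12 months:

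| Covariance | Baseline means free | Baseline means equal |
|---|---|---|
| Compound symmetry, r = 0.5 | 0.050 | 0.050 |
| SD 2, 0.5/0.4/0.6 | 0.084 | 0.069 |
| SD 2, 0.7/0.343/0.49 | 0.092 | 0.089 |
| SDs 1.5/2/2.5, 0.5/0.35/0.6 | 0.098 | 0.132 |
| SDs 2/2.5/2, r = 0.5 | 0.034 | 0.031 |
| SDs 2/2/1.5, r = 0.5 | 0.039 | 0.025 |

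The direction agrees with the formula in every scenario. The size depends somewhat on how baseline enters the model, which the article does not say.

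**The case against.** The strongest reply is that nothing in the article shows unequal variances or correlations, and that the sentence on the random intercept only says which effects are random. A random intercept does not exclude a structured residual or robust standard errors, and a fuller analysis plan, not shown here, may specify one. That stands as a limit: the point holds only if neither is added. It does not remove the point, because the random part is a stated choice and nothing in the article signals a residual structure.

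Several stronger readings are tempting and are not supported:

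- **That the model does understate the 12-month SE and inflate alpha.** Without visit-specific SDs or correlations this cannot be known, and the table contains conservative cases.
- **That the PSFS settles the direction.** Patients rate "up to three individual activities for which patients perceive limitations", so one might infer a compressed baseline variance. The article reports no such compression. With SDs 1.5/2/2 and equal correlations, it would make the 12-month test slightly conservative (0.042).
- **That alpha is 0.05 only under exact compound symmetry.** The 12-month test is nominal whenever V(0,12) equals Vmean, as in the last row of the first table.
- **That the treatment estimate is biased under dropout.** Likelihood estimates under missingness at random do rely on the covariance model, but no bias was quantified here; the simulations used data missing completely at random.
- **That 12 months is the key contrast.** The article lists 4 and 12 months together.

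**Conclusion.** The concern holds as a conditional robustness point. The stated model makes the validity of the 0.05 test for each change contrast depend on an equal-variance, equal-correlation assumption for which the article gives no support. If correlation decays over the 4- and 8-month gaps, the 12-month SE is about 6 to 14% too small and alpha about 0.065 to 0.09 by the formula; simulation with dropout gave up to 0.098, or 0.132 in the most extreme case with equal baseline means. Under other covariances the 12-month test is conservative, at about 0.03 to 0.04, and the 4-month contrast can err in the opposite direction from the 12-month one. All these figures rest on assumed covariances, a patient-level intercept and independent, constant-variance residuals. A reader should not infer a proven alpha inflation or an invalid primary analysis.

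**What to change.** In the analysis plan, replace the patient random intercept with an unstructured 3×3 residual covariance over baseline, 4 and 12 months, fitted by REML with Kenward-Roger degrees of freedom, and report the between-arm change contrasts at 4 and 12 months from that model. With complete data and free baseline means, each contrast then uses the variance of its own change score, so the nominal level no longer depends on the pattern of variances and correlations. Prespecify a random intercept with robust standard errors as the fallback if the model does not converge.

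The cost is small. The matrix has six parameters against two for the random-intercept model (6 − 2 = 4 more), which 158 patients support easily, and the risk of non-convergence is low. Data collection and sample size do not change.

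### The one missing-data sensitivity analysis named in the article, unqualified multiple imputation, by default shares the primary model's missing-at-random assumption and so does not test informative dropout

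*Protocol article*

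**What the plan says.** All references are to the protocol article.

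- **Primary analysis** (Effectiveness of the intervention): a linear mixed model using the baseline, 4-month and 12-month measurements, with a random intercept and everything else fixed.
- **Missing-data check** (same section): "A sensitivity analysis will be performed by replacing missing values by multiple imputation". The article gives no imputation model, auxiliary variables or assumption about why values are missing.
- **Other analyses** (Statistical analysis): the per-protocol analysis, restricted in the intervention arm to patients with at least four sessions, concerns adherence and not missing outcomes.
- **Expected loss** (Sample size and power calculation): "With an estimated dropout rate of 20% after 1 year at least 79 patients per treatment arm need to be included". The Discussion reports that 86% of patients completed the pilot.
- **Blinding and outcome** (Allocation and blinding; Primary outcome): "patients and therapists cannot be blinded to allocation", and the PSFS is completed by the patient. The data analysts are not blinded either.
- **Efforts to limit loss** (Data collection; Statistical analysis): reminders, telephone calls, paper questionnaires on request, and follow-up whether or not a patient complies with treatment.

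**The concern.** A sensitivity analysis is useful when it relaxes the assumption that is in doubt. A likelihood-based mixed model gives valid estimates if dropout depends only on data that were observed. Multiple imputation in its default form needs the same kind of condition. Agreement between them therefore says little about whether dropout depends on the unseen outcome itself.

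The article gives several reasons to doubt that condition.

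- Patients rate their own functioning and know what they were allocated to, so a patient who found the therapy unhelpful may stop answering for a reason tied to the missing score.
- Reasons to keep responding may differ by arm: usual-care patients are offered the therapy after the study if still indicated.
- There are only two follow-up points, so a patient lost before month 4 leaves no post-baseline PSFS value from which to predict the missing ones.

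The intention-to-treat analysis includes everyone randomised, and for non-responders that inclusion rests entirely on the missing-data assumption. Because the analysts are unblinded, departures chosen after the results are known would carry little weight. That is why pre-specification matters.

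**Working it through.** **Inputs** (Sample size and power calculation, unless noted)

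- Minimally relevant difference: 1 PSFS point. Higher scores mean better functioning.
- "with a standard deviation (sd) of 2 points"
- "with an alpha of 0.05 and a power of 0.80". Two-sided testing is assumed, because sidedness is not stated.
- Dropout 20%; 79 patients per arm.
- Pilot loss: 100% − 86% = 14% (Discussion).

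**Step 1: reproduce the plan's sample size.** n per arm = 2 × (1.96 + 0.842)² × 2² / 1² = 62.8, rounded up to 63. Allowing for dropout, 63 / (1 − 0.20) = 78.75, rounded up to 79, or 158 in total. This matches the article, and the sample size is not in question.

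**Step 2: precision at 12 months.** With 20% missing, 79 × 0.80 = 63.2 patients per arm are observed. SE = 2 × √(2/63.2) = 0.356. The smallest significant difference is 1.96 × 0.356 = 0.697. Under missing at random, an observed difference of 1.0 has p = 0.005.

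**Step 3: effect of a departure in the intervention arm.** Let δ be how many points worse the missing intervention-arm patients are than missing at random predicts, with controls as predicted. Then:

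adjusted difference = observed difference − 0.20 × δ

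Each point of δ therefore moves the effect by 0.20, which is 20% of the minimally relevant difference. For an observed difference of 1.0, with the SE held at 0.356:

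| δ (points) | adjusted difference | p |
|---|---|---|
| 0 | 1.00 | 0.005 |
| 1.0 | 0.80 | 0.025 |
| 1.5 | 0.70 | 0.049 |
| 2.0 | 0.60 | 0.092 |

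**Step 4: tipping point.** δ = (observed difference − 0.697) / 0.20.

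- Observed 1.0: 0.303 / 0.20 = about 1.5 points, less than one SD.
- Observed 0.8: 0.103 / 0.20 = about 0.5 points.
- Observed 1.25: 0.553 / 0.20 = about 2.8 points.

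**Step 5: vary the missing fraction, observed difference 1.0.**

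- 14% missing: 67.9 per arm, SE = 0.343, tipping δ = (1 − 0.673) / 0.14 = about 2.3 points.
- 30% missing: 55.3 per arm, SE = 0.380, tipping δ = (1 − 0.745) / 0.30 = about 0.85 points.

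**Step 6: departures in both arms.** With 20% missing in each arm, adjusted difference = observed difference − 0.20 × (δ intervention − δ control). Shifts of the same sign offset each other. If control dropouts are also 1 point worse than predicted, the intervention-arm tipping shift rises from about 1.5 to about 2.5 points. With unequal dropout a common shift does not cancel: at 25% and 15% missing, a 1-point shift in both arms moves the difference by (0.25 − 0.15) × 1 = 0.10.

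The δ values are assumptions. Nothing in the article says how large the departures would be.

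**The case against.** A mixed model supported by multiple imputation is a conventional plan, and nothing in the section is false. The article condenses a fuller protocol (Trial status cites version 10), and a separate analysis plan may exist. Imputation details and further analyses often sit there. This limits the point to what the article names: a reader might infer that the trial has no analysis under other assumptions, and the article cannot show that. It does not remove the point, because the article chose a method and called it the sensitivity analysis, and that method is poorly suited to testing informative dropout.

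A reader might also infer that the two analyses must agree and that the check will reassure whatever the truth. That goes too far. The trial collects symptom severity, 4DSQ, SF-36, illness attitudes and beliefs, GP consultations, and baseline expectations. An imputation model using these would rest on a weaker condition than a model of PSFS alone, and the results could differ. It would still assume missing at random given those variables.

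Another tempting reading doubles the shift to 0.40 by letting dropouts depart in opposite directions in the two arms. The article gives no reason to expect this. Disappointed patients in either arm would plausibly do worse than predicted, and those shifts partly cancel. If only disappointed controls were lost, the planned analysis would understate the benefit.

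Two mitigating facts stand. The 20% is a planning figure, with less loss in the pilot, and the follow-up efforts are aimed at keeping disengaged patients. Both reduce the size of the problem; neither tests the assumption.

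**Conclusion.** The point holds for the article as written. Its one named missing-data sensitivity analysis leaves the doubtful assumption essentially untested, so agreement with the primary model should not be taken as evidence against informative dropout. The article itself claims no such robustness; the risk lies in how the check is later read.

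The size is moderate and depends on the assumptions. At the planned effect, a one-arm shift of about 1.5 points would overturn significance with 20% missing, against about 2.3 points with 14%. An observed difference of 0.8 would tip at about 0.5 points. These figures use a normal approximation, the planning SD of 2 and a fixed SE; a mixed model that gains precision from the repeated measurements would tip later. They do not show that the trial's result will be biased. This is a change that should be made, not a fatal flaw.

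**What to change.** Keep the multiple imputation and state that it assumes missing at random, with the variables in the imputation model. Then pre-specify arm-specific shifts to the imputed PSFS values: for example 0 to −2 points in the intervention arm, crossed with controls left at 0 and also shifted. Report the estimate and interval across the grid, and the shift at which the conclusion changes. If that point lies outside the grid, extend the grid or say so. Control-based (reference) imputation for intervention-arm dropouts is an alternative.

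Recruitment was still open when the article was submitted, so this could be fixed in the analysis plan before outcomes were complete. The cost is a few more runs of imputation code already planned, one more table and possibly a less favourable statement about robustness. The sample size stays at 79 per arm.
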